### Observations and examinations

After enrollment, PI or Co-I collect all data prospectively whenever feasible. Data include the following: (1) the patient’s background: gender, date of birth, height, body weight, complications, past medical history, etiology of heart failure, coronary risk factors (hypertension, dyslipidemia, diabetes, hyperuricemia, and age > 45 years), and history of present illnesses; (2) compliance to IP administration (records of the day on which the BCAA preparation was first prescribed and the day of the last prescription) and the number of visits to the hospital for cardiac rehabilitation (per week); (3) concomitant medications; (4) subjective symptoms (Borg scale during cardiac rehabilitation) and objective findings; (5) adverse events (AE)^a^: details of AE, date and time of AE onset and resolution, severity, treatments, outcome, assessment of severity, and causal relationship with IP will be entered into the medical records and EDC. Follow-up investigations will be performed, if necessary. The levels of severity are defined as follows: (1) mild: treatment is not required and IP administration can continue, (2) moderate: IP administration can continue with some treatment, and (3) severe: IP administration will be or should be discontinued.

Characteristic patient data includes following parameters (Table 1): (1) Vital signs: Blood pressure before the start of cardiac rehabilitation (before warm-up exercise), pulse rate (in sitting position), as well as blood pressure and pulse rate at the time of outpatient visits (in sitting position); (2) CPX^b^: AT workload, VO_2_ AT, peak VO_2_, and ΔVO_2_/Δ work rate (WR); (3) Complete blood count (CBC), biochemistry tests and blood plasma tests^c^: White blood cell, red blood cell, hemoglobin, hematocrit, platelet, total protein, albumin, cholinesterase, aspartate aminotransferase, alanine aminotransaminase, gamma-glutamyl transpeptidase, blood urea nitrogen, creatinine, C-reactive protein, and brain natriuretic peptide; (4) Cytokine blood tests^d^: TNF-α and IL-6; (5) Echocardiography^e^: left ventricular diastolic diameter (M mode), left ventricular EF (M mode), E/A, E/e’, and left atrial diameter; (6) Emotional outcome measure^f^: Total points of HADS; (7) Assessment of muscle strength^g^: Grip strength and lower-limb extension power; (8) Events of hospitalization because of heart failure during the study period.

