### Study methods

This is a randomized, active-controlled, parallel-group comparative study. Study outline is presented in Fig. 1. The study consists of three periods—pre-observation, intervention with concurrent cardiac rehabilitation, and BCAA single intervention. In pre-observation period (Day 1 to Week 4), the consent of patients undergoing cardiac rehabilitation at the hospital for CHF will be obtained, and their eligibility will be determined by blood tests and imaging tests (echocardiogram). In the period of intervention with concurrent cardiac rehabilitation (for 18–22 weeks), patients who are confirmed eligible for study enrollment will be randomized into either group A (CR + BCAA) or group B (CR). BCAA is orally supplemented with one pack of BCAAs granules (Aminovact Combination Granules ®, Nichi-Iko Pharmaceutical Co, Toyama, Japan) which includes 1144 mg of L-valine, 1904 mg of L-leucine and 952 mg of L-isoleucine, two times a day. Cardiopulmonary exercise test (CPX) will be performed on each subject in both groups before intervention with the BCAA preparation as well as at Week 14 and Week 20 of the intervention with cardiac rehabilitation. In the BCAA preparation single intervention period (20–24 weeks), re-randomization, i.e., randomization 2, will be performed after the cardiac rehabilitation program has ended. Subjects in group A will be assigned to Group A-1 or A-2, whereas those in Group B will be assigned to Group B-1 or B-2. As described in Fig. 1, subjects assigned to Group A-1 will continue the BCAA preparation. Similarly, subjects in Group B-1 will start taking the BCAA preparation. The BCAA preparation will be discontinued for subjects assigned to Group A-2, and subjects in Group B-2 will not undergo intervention with the BCAA preparation throughout the study period.

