### Outcome measures

Primary outcome measure is the rate of change of the AT workload from baseline to post-intervention with concurrent cardiac rehabilitation. Secondary outcome measures include the following: (1) The rate of change from baseline which is performed in the pre-observation period or reference day [Peak VO_2,_ left ventricular EF in the echocardiogram, total points of the Hospital Anxiety and Depression Scale (HADS), muscle strength (grip strength and lower-limb extension power), absolute values of interleukin-6 (IL-6), and tumor necrosis factor (TNF)-α], Time taken for 50% subjects to achieve a 15% improvement in AT workload, which is defined as an event. (2) The rate of change from post-intervention period with cardiac rehabilitation (20 weeks later) to post-single intervention with the BCAA preparation (32 weeks later) [Peak VO_2_, AT workload, total points of HADS, muscle strength (grip strength and lower-limb extension power))], (3) The frequency of serious adverse events (SAEs) throughout the study period.

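### Severe adverse events are defined only by stopping IP, so the grade has no stated meaning for patients not taking it; whole-study SAE counts also mix BCAA exposure after the second randomization

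*Protocol article*

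**What the plan says.** Under Observations and examinations, the protocol article sets out three severity levels for adverse events. The lowest is "1) mild: treatment is not required and IP administration can continue". The middle level covers events that need some treatment while IP goes on. The highest is "3) severe: IP administration will be or should be discontinued". IP is evidently the BCAA preparation, because the compliance item in the same section is recorded through BCAA prescription dates.

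Under Study methods, patients "will be randomized into either group A (CR + BCAA) or group B (CR"), and no placebo is described. At the second randomization A-1 continues BCAA, B-1 starts it and A-2 stops it. Of the fourth subgroup the article says: "subjects in Group B-2 will not undergo intervention with the BCAA preparation throughout the study period".

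Under Outcome measures, one secondary outcome is "The frequency of serious adverse events (SAEs) throughout the study period".

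On timing, Study methods gives 18–22 weeks for the rehabilitation period and 20–24 weeks for the BCAA-only period, while Outcome measures places the end of rehabilitation at 20 weeks and the end of the BCAA-only period at 32 weeks. Onset and resolution dates of adverse events are recorded, as are the first and last prescription days.

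**The concern.** A severity scale should mean the same thing in every group. This one refers to IP in all three grades, in an open trial whose control patients have no IP to continue or stop. An investigator grading an event in group B has to improvise the severe category, knowing the allocation. Among treated patients the scale merges how bad an event was with what was done about the study product. A mild event that leads to stopping IP is graded severe, while an intense event that is treated with IP continuing is graded moderate. A table of severity by group would then not compare like with like.

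The SAE point is separate, because seriousness and severity are different concepts and the grading does not alter the SAE count. A count over the whole study contains time on and off BCAA in both original groups. An A versus B reading of it would pull a true effect of BCAA on SAEs towards no difference, which is the unfavourable direction for safety.

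**Working it through.** **Severity scale.** Setting the grades against the treatment groups:

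| Grade | Criterion apart from IP | Can it be applied to a patient off IP? |
|---|---|---|
| Mild | No treatment needed | Partly, by need for treatment |
| Moderate | Some treatment needed | Partly, by need for treatment |
| Severe | None | Only as a hypothetical: would IP have to stop if the patient were taking it? |

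Patients off IP are group B in the first period, A-2 and B-2 in the second. No allocation ratio is stated. If both randomizations are 1:1, that is one half in each period, or 24 of the target 48 patients before dropout.

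**SAE window.** The plan states no figure here to reproduce. Let P1 and P2 be the lengths of the two periods, and assume a 1:1 second randomization. The share of follow-up assigned to BCAA is

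- group A: (P1 + 0.5 × P2) / (P1 + P2)
- group B: 0.5 × P2 / (P1 + P2)
- difference: P1 / (P1 + P2)

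With P1 = 20 weeks (nominal):

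| Reading of the second period | P2 | Group A | Group B | Difference |
|---|---|---|---|---|
| Ends at week 32 (Outcome measures) | 12 | 26/32 = 81% | 6/32 = 19% | 62.5 points |
| Lasts 20 weeks (Study methods, as a duration) | 20 | 30/40 = 75% | 10/40 = 25% | 50 points |
| Lasts 24 weeks (Study methods, as a duration) | 24 | 32/44 = 73% | 12/44 = 27% | 45 points |
| Study weeks 20 to 24 (Study methods, as calendar) | 4 | 22/24 = 92% | 2/24 = 8% | 83 points |

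Letting P1 run from 18 to 22 weeks and P2 from 12 to 24 gives 18/42 = 43 to 22/34 = 65 points. A count restricted to the first period has the full 100 points.

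**Illustration.** Assume a true on/off SAE rate ratio of 2.0, a constant background rate and no carry-over. With 20 + 12 weeks, A versus B would show (0.1875 + 0.8125 × 2) / (0.8125 + 0.1875 × 2) = 1.8125 / 1.1875 = 1.53. With a second period of 20 or 24 weeks it would show 1.40 or 1.36. The ratio of 2.0 is chosen only to show the size of the dilution; the article gives no SAE rates.

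**The case against.** A reader might infer that half the patients cannot be graded at all. The text does not support that. Need for treatment separates mild from moderate in anyone, and the wording that IP should be stopped can be applied hypothetically. This objection stands, and it confines the defect to the severe grade and to the mixing of intensity with action. It does not remove the defect, since a hypothetical judgement by an investigator who knows the allocation is not a common scale.

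It is also fair that severity is not a listed outcome and that no severity comparison is planned, so no primary or secondary endpoint is affected. The adverse-event item carries a footnote marker whose text is not in the copy read here, and it may add detail. However, the three levels are presented as the definition of severity, not as an extract of a longer scale.

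On SAEs, a reader might infer that the plan commits to a whole-study A versus B t-test that would hide harm from BCAA. The document does not say so. The outcome names no contrast. The t-test for secondary endpoints in Statistical considerations is worded for percentage differences, which fits the rate-of-change outcomes better than event counts. That section also compares B-1 with B-2, includes both randomizations as factors in an ANOVA and plots four groups. Counting SAEs throughout a study is ordinary safety scope, tabulation is commonly left to the analysis plan, and the dates needed for a split are collected. All of this stands, so the SAE point is conditional and secondary.

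**Conclusion.** The severity point holds on the text alone. The severe grade rests entirely on stopping IP and has no stated meaning for group B during rehabilitation, A-2 afterwards or B-2 throughout. Under assumed equal allocation that is about half the patients at any time. Severity as defined is therefore not comparable between groups, though mild and moderate keep some meaning off IP. The effect is on descriptive safety reporting, not on a planned test.

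The SAE point holds conditionally. If the whole-study count is compared between A and B, the exposure difference is about 62 points with 20 + 12 weeks, 45 to 50 if the 20–24 weeks in Study methods is a duration, and about 83 if it means study weeks. These figures assume 1:1 allocation, a first period of 20 weeks and follow-up as assigned. Under every reading the difference is below 100. The two statements of the second period's length must be reconciled before any one figure can be relied on.

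**What to change.** 1. Define adverse-event severity by clinical intensity, in terms that apply identically to all groups and both periods.
2. Record action taken with IP as a separate field, completed only for patients on IP. This concerns how events are recorded; it proposes no rule on when IP should be stopped.
3. State that SAEs will be tabulated by period and by treatment assigned in that period: A versus B up to the second randomization, then A-1 versus A-2 and B-1 versus B-2. Give patients with events and person-time. A whole-study total can be kept as a descriptive line.
4. Reconcile the length of the second period between Study methods and Outcome measures.

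The cost is one changed case report form definition, one added field and a few table shells, with minor retraining of investigators and recoding of events already graded. The SAE split needs no new data, because onset dates are already collected.

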**Table 1 Tab1:**
[figure not shown]
Study schedule

○ Indicates items that occur before administration of BCAA

● Indicates items that occur after administration of BCAA

※ Indicates items that occur after suspension of the study

### Statistical considerations

The sample size was calculated according to the estimation as follows. We hypothesized that following 6 months of cardiac rehabilitation, there will be an AT workload improvement of 25% (SD: 10%). With the addition of BCAA, we hypothesized that there will be an AT workload improvement of 25% (SD: 10%). Setting the two-sided significance level at5% and power at 90%, the required sample size was 43 cases. Assuming a 5% rate of subjects leaving the study, we chose 48 cases as the target number.

According to the study results, differences (%) in primary outcome between each outcome measurement between A and B groups will be evaluated using the t-test. With respect to differences in outcome measurement (%) in secondary endpoint between groups A and B, the t-test will be used to analyze statistical significance. Similarly, the difference between B-1 and B-2 sub-groups will be analyzed using the t-test. Also,, after confirming the assumption that there are no major differences among the treatment groups (no interaction), the two-way ANOVA will be used to test the treatment effect for addition of a BCAA, and maintenance effect for continuing administration of a BCAA by including group A/B and +1/+2 as factors. A box-plot will be used to visualize primary outcome and secondary outcomes between the 4 groups (A + 1, A + 2, B + 1, B + 2). Finally, defining an AT workload improvement of 15% as an event, a Kaplan–Meier curve will be plotted to compare the curves between groups A and B, and estimate the occurrence of an event rate of 50% of each group.

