### Enrollment and assignment

PI or Co-I will obtain the written consent of subjects. The enrollment of subjects who have given their consent and the data of all subjects will be entered into the electronic data capture (EDC) system (Viedoc, PCG Solutions, Uppsala, Sweden). For randomization 1, the subjects will be stratified into two groups (groups A and B as mentioned earlier) according to (1) age (>70 or ≤70 years) and (2) anaerobic threshold (AT) workload (≥30 watts or <30 watts) in the first CPX performed at the time of consent-taking. Randomization 2 will be performed after the intervention period with concurrent cardiac rehabilitation has ended. The stratification factors are (1) the age of the subject (>70 or ≤70 years) and (2) the rate of change in the AT workload in CPX after intervention with concurrent cardiac rehabilitation has ended (≥25% or <25% for group A and ≥15% or <15% for group B).

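### The sample-size paragraph prints the same 25% (SD 10%) improvement for both arms, so 43 cases and 90% power cannot follow from the stated assumptions

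*Protocol article*

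**What the plan says.** All the design inputs stand in one paragraph of the protocol article, under Statistical considerations.

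- CR alone: "We hypothesized that following 6 months of cardiac rehabilitation, there will be an AT workload improvement of 25% (SD: 10"%).
- CR plus BCAA: "With the addition of BCAA, we hypothesized that there will be an AT workload improvement of 25% (SD: 10"%).
- Error rates and result: "Setting the two-sided significance level at5% and power at 90%, the required sample size was 43 cases".
- Inflation: "Assuming a 5% rate of subjects leaving the study, we chose 48 cases as the target number".
- Primary analysis: the difference "between A and B groups will be evaluated using the t-test".

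One other place bears on the assumed effect. Under Enrollment and assignment, randomization 2 is stratified by the change in AT workload at the end of the rehabilitation period, with cut-offs that differ by arm: "≥25% or <25% for group A and ≥15% or <15% for group B". The article nowhere states a target difference, a different assumed mean for either arm, or a non-inferiority or equivalence margin.

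**The concern.** The aim is superiority: whether BCAA adds to what conventional rehabilitation achieves. A superiority calculation needs a non-zero difference, and the two printed means are identical. The stated size and power therefore contradict the stated inputs.

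This paragraph is the only basis given for the trial's size. If the assumed effect is wrong on the page, a reader cannot check the power claim. Nor can a reader say with confidence what size of effect a null result on the primary outcome would speak against.

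**Working it through.** **Inputs.** Means 25% and 25%, SD 10% in each arm, two-sided alpha 5%, power 90%, two-sample t-test, 5% loss, target 48 (all from Statistical considerations). Two things are assumed. Allocation is taken as 1:1, because the article gives no ratio. The 43 is taken as a total, which fits a target number of 48 cases for the trial.

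**Step 1: the plan's figure from the printed inputs.** The normal-approximation formula is

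n per group = 2 × (1.960 + 1.2816)² × (SD / difference)².

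With difference = 25 − 25 = 0 the formula divides by zero, so no finite n exists. The rejection probability of the t-test is 0.05 at 21 + 22 and at 24 + 24 alike. The figure 43 is not reproduced. Changing the power, using a one-sided test or reading 43 as per group does not help, because the difference stays at zero.

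**Step 2: what difference 43 implies.** Solving for the difference with 21 + 22 patients:

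10 × (1.960 + 1.2816) × √(1/21 + 1/22) = 9.89 points.

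In the other direction, a 10-point difference gives 2 × (3.2416)² × (10/10)² = 21.01 per group, 42.03 in total. Rounding the total up gives 43.

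**Step 3: the planned t-test at a 10-point difference, SD 10%** (noncentral t, two-sided 5%):

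| Analysed | Split | Power |
|---|---|---|
| 43 | 22/21 | 0.893 |
| 44 | 22/22 | 0.8997 |
| 45 | 23/22 | 0.906 |
| 46 | 23/23 | 0.912 |
| 48 | 24/24 | 0.924 |

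With equal groups, 46 is the smallest total that reaches 90%. With 48 enrolled and 5% lost, 48 × 0.95 = 45.6, so about 45 are analysed and power is about 90.6%.

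**Step 4: sensitivity to the unstated difference.** At 5 points with SD 10%, the normal approximation needs 85 per group (170 in total) and the t-test 86 per group (172). With 43 analysed, t-test power is about 0.36.

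**Step 5: the inflation.** 43 / 0.95 = 45.3, so 46, not 48. Two routes come close to 48. The t-test requirement of 46 inflated by 5% gives 46 × 1.05 = 48.3 or 46 / 0.95 = 48.4. Alternatively, 46 may have been rounded up, for example to a multiple of four. The article names neither.

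**The case against.** The strongest reply is that this is a misprint with no effect on the trial. The printed 43 leads back to a difference of about 10 points, the arm-specific cut-offs of 25% and 15% fit it, and on that reading 48 enrolled gives just over 90% power after the stated loss. Most of this stands. A reader might infer from the identical means that the trial was designed with no effect in view, or that it is underpowered. The documents do not support either inference: a figure of 43 cannot come from a zero difference, so some other value was evidently used.

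The reply does not remove the point, because the intended value still has to be guessed. A reader might also take 15% for CR alone as established. It is not. The size depends only on the difference, so 25% against 35% gives 43 just as well as 15% against 25%. The cut-offs are stratification factors for randomization 2, not design assumptions. The article also uses 15% as the event threshold for the Kaplan–Meier comparison in both arms, so that value is not specific to control.

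Two related points are minor. The shortfall from using the normal approximation is under one percentage point of power at 43 on the 10-point reading (0.893 against 0.90). The surplus from 46 to 48 errs on the safe side.

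**Conclusion.** The point holds as an error in the stated assumptions. As printed, the planned difference is zero, and 43 cases with 90% power at two-sided 5% do not follow from it. The most likely cause is a misprinted mean for CR alone, in a trial of about the right size for a 10-point difference: 89.3% power with 43 analysed and 90.6% with 45.

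That reassurance rests on four assumptions: a 10-point difference, SD 10% in both arms, 1:1 allocation, and 43 as a total. The first matters most and is the one the article leaves unstated. At 5 points the power with 43 would be about 36%.

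**What to change.** The sponsor should go back to the calculation actually made and print the mean assumed in each arm, the target difference and the SD. The 15% value should not be adopted merely because it fits.

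The size and power should then be restated for the planned t-test, with the allocation ratio and the number per group. If the difference is confirmed as 10 points with 1:1 allocation, the text can say that 23 per group (46 in total) gives at least 90%, and that 48 enrolled with 5% loss leaves about 45 analysed and about 90.6% power. One clause should say how 48 was reached: the t-test requirement of 46 inflated by about 5%, or rounding.

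In that case the cost is corrected wording and no extra patients. If the difference actually assumed was smaller, the size and the power claim would have to be worked out again.

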### Aim

The primary objective of this study is to explore whether the addition of a BCAA preparation for cardiac rehabilitation of patients with CHF further improves cardiopulmonary functions, skeletal muscle functions, and metabolism in comparison with conventional cardiac rehabilitation. In addition, we will also explore whether continued administration of a BCAA preparation after cardiac rehabilitation can preserve cardiopulmonary and skeletal muscles functions.

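### The continuation aim is tested only through a pooled factor that mixes continuers with starters, and it depends on a no-interaction assumption that about 12 patients per cell cannot verify

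*Protocol article*

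**What the plan says.** The Aim section of the Protocol article states the second question: "we will also explore whether continued administration of a BCAA preparation after cardiac rehabilitation can preserve cardiopulmonary and skeletal muscles functions".

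Study methods describes the second randomization, made within each original group:

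- A-1: "subjects assigned to Group A-1 will continue the BCAA preparation".
- A-2: "The BCAA preparation will be discontinued for subjects assigned to Group A-2".
- B-1: "subjects in Group B-1 will start taking the BCAA preparation".
- B-2: no BCAA at any time.

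Outcome measures defines the second-period endpoints as "The rate of change from post-intervention period with cardiac rehabilitation (20 weeks later) to post-single intervention with the BCAA preparation (32 weeks later"), covering peak VO2, AT workload, HADS and muscle strength.

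Statistical considerations gives the analysis. The subgroup t-test is "Similarly, the difference between B-1 and B-2 sub-groups will be analyzed using the t-test". A two-way ANOVA follows, to be used once absence of interaction has been confirmed. It is to test the effect of adding BCAA and the "maintenance effect for continuing administration of a BCAA by including group A/B and +1/+2 as factors". The four groups are also to be shown in box-plots.

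**The concern.** Only patients who took BCAA in the first period can continue it. The randomized comparison that isolates continuation is therefore A-1 versus A-2, and no test of it is named. The t-test that is named, B-1 versus B-2, compares first use without rehabilitation with no use.

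The effect labelled as maintenance sets A-1 and B-1 together against A-2 and B-2. With equal cells, half of its weight comes from patients who have nothing to continue. It equals the continuation effect only if starting and continuing work equally well, so the answer to the second aim depends on how well the trial can check that.

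The risk is a wrong statement about continuation in either direction: maintenance claimed when only starters gained, or a real continuation effect diluted. If interaction is found, the article states no analysis of continuation.

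**Working it through.** **Inputs from the article (Statistical considerations; Enrollment and assignment)**

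- Target 48 patients, 5% leaving the study, two-sided 5% level.
- SD 10% for the first-period AT workload improvement.
- Cut-offs of 25% (group A) and 15% (group B) for stratifying randomization 2.

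**Assumptions**

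- 1:1 allocation at both randomizations: 48/4 = 12 per cell, or 48 × 0.95/4 = 11.4, taken as 11, after losses.
- SD 10 for the week-20 to week-32 change. The article gives no SD for this period, so a range is shown below.
- Interaction checked by a two-sided 5% test. The article does not say how it will be confirmed.
- An effect of 10 points, for scale.

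**The plan's own figure.** The printed assumptions are 25% in both arms, a difference of 0, from which no finite sample size follows. If the difference is taken as 25 − 15 = 10 from the stratification cut-offs, the total is 4 × (1.960 + 1.282)² × (10/10)² = 42.03, which rounds up to the stated 43. This is why 10 points is used here. The printed 25% versus 25% is a separate matter.

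**What each contrast estimates.** Let a = A-1 minus A-2 (continuing) and b = B-1 minus B-2 (starting).

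- Pooled +1/+2 effect = (a + b)/2, SE = SD × √(1/n), df = 4n − 4.
- Direct continuation contrast = a, SE = SD × √(2/n), df = 2n − 2.
- Interaction = a − b, SE = SD × √(4/n), df = 4n − 4.

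For SD 10 the standard errors at n = 11 and n = 12 are:

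- pooled: 3.02 and 2.89;
- direct: 4.26 and 4.08;
- interaction: 6.03 and 5.77.

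**Power from the noncentral t, SD 10**

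| Quantity | n = 11 | n = 12 |
|---|---|---|
| Interaction test, a − b = 10 | 37% | 40% |
| Interaction test, a − b = 5 | 13% | 14% |
| Pooled effect, a = 10, b = 0 (estimates 5) | 37% | 40% |
| Direct A-1 vs A-2, a = 10 | 61% | 65% |
| Direct A-1 vs A-2, a = 5 | 20% | 22% |
| Pooled effect, a = b = 10 | 90% | 92% |

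**Only starters benefit (a = 0, b = 10).** The pooled effect is (0 + 10)/2 = 5 points. At n = 12 the interaction is missed in about 60% of trials. In a simulation of 100,000 trials, about 23% had a non-significant interaction together with a significant pooled effect. A rough check that treats the two tests as independent gives 0.605 × 0.395 = 0.24.

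**Range of SD, 10-point effects, n = 11 and n = 12**

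| SD | Direct A-1 vs A-2 | Interaction test | Pooled, a = b = 10 |
|---|---|---|---|
| 10 | 61%, 65% | 37%, 40% | 90%, 92% |
| 15 | 32%, 35% | 19%, 20% | 58%, 62% |
| 20 | 20%, 22% | 13%, 14% | 37%, 40% |

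A larger SD weakens every analysis, including the interaction check on which the pooled one depends.

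**Precision of the direct contrast at SD 10.** The expected 95% half-width is about 2.086 × 4.26 = 8.9 points at n = 11 and 2.074 × 4.08 = 8.5 points at n = 12. For a 10-point difference, 80% power needs 17 per cell and 90% needs 23.

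**The case against.** A reader might infer that the second aim goes unanswered, or that the trial, followed as written, must report a maintenance effect that is not one. The text does not support either. The article assigns the maintenance question to an analysis and makes that analysis conditional on no interaction. Where that condition is true, a = b, so the pooled effect is the continuation effect and is estimated far more efficiently (90–92% power against 61–65% for 10 points at SD 10). That is the ordinary case for a factorial main effect, and it stands.

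Nor is B-1 versus B-2 a misplaced test. The Discussion presents the second period as a way to separate the effect of the nutrition itself from its effect added to training, and this contrast addresses that. The second randomization is stratified separately within group A, so A-1 versus A-2 remains a valid randomized comparison, and the box-plots will display it.

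The aim is worded as exploratory and its endpoints are secondary. A full protocol or analysis plan could carry further contrasts. The direct contrast is itself weak.

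What this does not remove is the reliance on confirming no interaction. A test with 37–40% power for a 10-point difference cannot do that. Nor is equality of effects an obvious default: stopping after months of use during training is a different exposure from first use without training. The label on the pooled factor is the article's own choice, so it is not a detail left to another document.

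**Conclusion.** The point holds in limited form. The article answers the continuation aim indirectly, through an average of continuing and starting effects. That average equals the continuation effect only under an assumption the trial is too small to confirm. The randomized contrast that needs no such assumption is not named.

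With 1:1 allocation, 11 to 12 per cell and an assumed second-period SD of 10%, the consequence depends on the true pattern:

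- a false maintenance claim in about 23% of trials if only starters gain 10 points;
- a halved estimate if only continuers gain 10 points;
- no bias if both gain equally.

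The algebra of the contrasts does not depend on the SD, but the percentages do. Severity is moderate, because the aim is secondary and exploratory and the primary A versus B test is untouched.

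**What to change.** In Statistical considerations:

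1. Name A-1 versus A-2 on the week-20 to week-32 outcomes, reported as an estimate with a 95% confidence interval, as the exploratory analysis of the continuation aim.
2. Keep B-1 versus B-2 as the analysis of starting BCAA without rehabilitation.
3. Keep the pooled +1/+2 effect as supportive only. Describe it as the average effect of BCAA in the second period, not as a maintenance effect.
4. Report the interaction estimate with its confidence interval, and state that a non-significant test will not be taken as confirming no interaction.

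The cost is wording and one further contrast on data already being collected. Design, sample size and conduct do not change. The downside is a wide interval for A-1 versus A-2, about ±8.5 to 8.9 points at SD 10 and wider if the SD is larger. The text should say so.
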